## Abstract

**Background:**

Deep inspiration breath hold (DIBH) reduces radiotherapy cardiac dose for left-sided breast cancer patients. The primary aim of the BRAVEHeart (Breast Radiotherapy Audio Visual Enhancement for sparing the Heart) trial is to assess the accuracy and usability of a novel device, Breathe Well, for DIBH guidance for left-sided breast cancer patients. Breathe Well will be compared to an adapted widely available monitoring system, the Real-time Position Management system (RPM).

**Methods:**

BRAVEHeart is a single institution prospective randomised trial of two DIBH devices. BRAVEHeart will assess the DIBH accuracy for Breathe Well and RPM during left-sided breast cancer radiotherapy. After informed consent has been obtained, 40 patients will be randomised into two equal groups, the experimental arm (Breathe Well) and the control arm (RPM with in-house modification of an added patient screen). The primary hypothesis of BRAVEHeart is that the accuracy of Breathe Well in maintaining the position of the chest during DIBH is superior to the RPM system. Accuracy will be measured by comparing chest wall motion extracted from images acquired of the treatment field during breast radiotherapy for patients treated using the Breathe Well system and those using the RPM system.

**Discussion:**

The Breathe Well device uses a depth camera to monitor the chest surface while the RPM system monitors a block on the patient’s abdomen. The hypothesis of this trial is that the chest surface is a better surrogate for the internal chest wall motion used as a measure of treatment accuracy. The Breathe Well device aims to deliver an easy-to-use implementation of surface monitoring. The findings from the study will help inform the technology choice for other centres performing DIBH.

**Trial registration:**

ClinicalTrials.govNCT02881203. Registered on 26 August 2016.

**Supplementary Information:**

The online version contains supplementary material available at 10.1186/s13063-023-07072-y.

## Administrative information

Note: the numbers in curly brackets in this protocol refer to SPIRIT checklist item numbers. The order of the items has been modified to group similar items (see http://www.equator-network.org/reporting-guidelines/spirit-2013-statement-defining-standard-protocol-items-for-clinical-trials/).

## Introduction

### Background and rationale {6a}

Radiotherapy is recommended for 87% of all diagnosed breast cancer patients for disease control [1], but it can lead to late cardiac side effects [2]. Deep inspiration breath hold (DIBH) increases the lung volume and moves the heart outside of the irradiation fields, reducing the heart dose [3–7] and thus reducing the cardiac toxicity during breast cancer radiotherapy [2, 8, 9]. Nissen et al. [7] estimated that DIBH reduces the mean heart dose from 5.2 to 2.7 Gy on average and Darby et al. [2] concluded that the rate of major coronary events increased linearly by 7.4% per Gray of mean heart dose with no threshold. The Darby data outlines that it is important to keep the dose to the heart from radiotherapy, especially for young patients, as low as possible and based on their analysis DIBH reduces the increased rate of major coronary events due to the radiation treatment by 20% [2].

Standardly the patients are guided to the breath hold level with audio prompts from the operating radiation therapists. However, Cervino et al. [10] demonstrated that providing the patients with visual feedback by adding a monitor or goggles in addition to audio guidance has demonstrated improvement in the reproducibility of DIBH by 95% and stability by 80% (and for variations >2 mm by 35% and 15%, respectively). Similar findings have been reported by Damkjær et al. [11].

Several systems are currently commercially available to assist the implementation of DIBH in the clinic. These systems include the real-time position management (RPM) system and real-time gating for scanners (RGSC) system (Varian Medical Systems, Palo Alto, CA), the active breathing coordinator (ABC) (Elekta, Stockholm, Sweden), AlignRT (Vision RT Inc., London, UK), Catalyst HD (C-RAD, Uppsala, Sweden), Exac-Trac (Brainlab, Feldkirchen, Germany), and Identify (Varian Medical Systems, Palo Alto, CA).

RPM and RGSC utilise an infrared camera tracking a marker block, standardly placed on the abdomen between the xiphoid process and the umbilicus. ABC uses a spirometer with a valve that is closed for the breath hold. AlignRT, Catalyst HD, Exac-Trac and Identify use 3D surface imaging, requiring in-room installation and/or do not standardly include a visual feedback feature.

Breathe Well (Fig. 1) is a new audiovisual (AV) feedback device developed at the University of Sydney that may increase the efficacy and improve the workflow of implementing DIBH for breast cancer patients. Breathe Well is clamped on the superior end of the computed tomography (CT) couch or treatment couch and uses depth and optical sensors to directly monitor a user-defined area on a patient’s chest. The positional accuracy and precision of the depth sensor has been shown to be within ± 1.0 mm and the temporal stability of the sensor is sub-mm [12]. The horizontal and vertical axes of the device can be adjusted to fit the patient and immobilisation device dimensions and the device arm can be rotated to enable an unobstructed patient setup and an optimal view of the included screen when the patients are treated with their head tilted (Fig. 1A). The monitoring region of interest is selected by the radiation therapist from within the optical field of view e.g. centred on the sternal tattoo and corresponds to an area of a few square centimetres on the patient’s chest. Within the Breathe Well software application a patient-specific reference breath hold with respect to the normal breathing baseline can be measured and stored. The included screen delivers real-time feedback to the patient regarding their chest position. The breath hold target area (gating window) is highlighted and depending on the workflow status the screen (Fig. 1B) shows an orange wait screen or instructs the patient to hold their breath or relax. An optional breath hold countdown option helps the patient to see how long they still have to hold their breath. At their workstation, the radiation therapists also see the real-time visual feedback indicating when the breath hold depth is acceptable, allowing them to control treatment delivery.

**Fig. 1 Fig1:**
[figure not shown]
The Breathe Well device. **A** Similar setup on the CT and treatment couch. **B** Patient screen with breath hold position visualisation and instructions. **C** Optical feed and breath-hold depth monitoring central chest area displayed to the radiation therapist

RPM and RGSC (Fig. 2) similarly have a positional accuracy quoted by the manufacturer of ± 1.0 mm. The RPM system is installed in the CT simulation suite and uses an infrared camera clamped to the foot of the couch while the RGSC system is installed in the treatment suite, with the infrared camera fixed to the ceiling. These infrared cameras monitor a block with reflective dots placed on the patient. For breast DIBH treatment this is commonly placed near the xiphoid process so as to ensure it is not within the treatment field. As with Breathe Well, a patient-specific reference breath hold with respect to the normal breathing baseline can be measured and stored. However, visual feedback is not standardly provided to the patient by these systems, though visualisation of the breathing motion is provided to the radiation therapists. An in-house visual feedback screen has been produced to replicated this real-time breathing visualisation for the patient. In this visualisation, a yellow bar moves up and down to show the anterior-posterior motion. The target gating window is represented as a blue region with the bar changing colour when within the region (Fig. 2C). RPM and RGSC are integrated with the treatment machine to automatically gate the beam.

**Fig. 2 Fig2:**
[figure not shown]
The RPM and RGSC systems. **A** RPM system used at CT. **B** RGSC used during linac treatment. **C** Patient screen with breath hold position visualisation. **D** Camera and marker block setup at CT. **E** Camera and marker block setup at treatment

The primary aim of this study is to test the accuracy and usability of Breathe Well to assist DIBH during breast cancer radiotherapy.

### Objectives {7}

The primary objective of the study is to test the accuracy and usability of Breathe Well to assist DIBH during breast cancer radiotherapy. Breathe Well will be tested against the commercially available real-time position management (RPM) / respiratory gating for scanners (RGSC) system (Varian Medical Systems, Palo Alto, CA), which has been extended in-house to provide a screen for visual feedback.

The primary hypothesis is that the accuracy of Breathe Well in maintaining the position of the chest during DIBH is superior to the RPM/RGSC system. Because Breathe Well monitors the chest directly, while the RPM/RGSC system uses a marker block positioned on the upper abdomen, Breathe Well has the advantage of utilising a more immediate surrogate of the chest wall position. In addition, we hypothesise that Breathe Well is more user-friendly as it was specifically designed for guiding breast cancer patients through DIBH treatments.

Secondary objectives:To measure the setup times for both the Breathe Well and the modified RPM/RGSC system for all fractions. We hypothesise that Breathe Well can be set up faster than the modified RPM/RGSC system.To investigate patient comfort and user friendliness of Breathe Well via a patient survey (Supplementary Materials). We hypothesise that the patient comfort and usability of Breathe Well is superior to the Varian RPM system.To investigate staff perception of Breathe Well via a technology assessment survey (Supplementary Materials). We hypothesise that the staff perception of Breathe Well is superior to the Varian RPM/RGSC system.To develop — offline — the use of the electronic portal imaging device (EPID) for real-time MLC tracking during monitoring the chest wall position in breast radiotherapy.To investigate, using dose reconstruction, the estimated dose delivered during radiotherapy and compare this with the planned dose.

### Trial design {8}

The trial design is a randomised, prospective superiority trial with an experimental (breathe well) and a control (RPM/RGSC) arm allocation ratio 1:1. Patients receiving radiotherapy for left-sided breast cancer will be randomised into two equal groups. The experimental arm will manage breath holds with audiovisual biofeedback from the Breathe Well device. Patients in the control arm will manage breath holds using an in-house developed audiovisual feedback for the RPM/RGSC system. The trial schema is summarised in Fig. 3.

**Fig. 3 Fig3:**
[figure not shown]
The BRAVEHeart study schema

## Methods: participants, interventions and outcomes

### Study setting {9}

Study participants will be recruited and treated at the Royal North Shore Hospital, St Leonards, NSW, 2065, Australia.

### Eligibility criteria {10}

Inclusion — patientsLeft-sided breast cancer patients (invasive and in situ)To be treated in the supine positionAbility to perform a ≥ 20-s breath hold> 18 years oldFemaleAn ECOG score from 0 to 2Able to read and complete questionnaires in EnglishAble to give written informed consent and willingness to participate and comply with the study

Exclusion — patientsNo regional lymph nodes involved or at riskNo pregnant/lactating women

### Who will take informed consent? {26a}

Potential participants will be identified by their consulting clinician who will explain the study, including risks and benefits and give the opportunity for informed discussion. They will receive a copy of the informed consent form to carefully read and take home for further analysis if necessary. Trained clinical trials staff at Royal North Shore Hospital will obtain informed consent from patients prior to their CT simulation appointment.

### Additional consent provisions for collection and use of participant data and biological specimens {26b}

Not applicable.

## Interventions

### Explanation for the choice of comparators {6b}

The choice was made to compare the novel Breathe Well device to RPM/RGSC as an existing widely adopted commercial system in clinical use for breath hold management.

### Intervention description {11a}

Training and simulation: The patients will be trained to perform DIBH with the assigned system and assessed for ability to perform a 20-s breath hold (at 80–90% of the maximal lung capacity). Based on this screening the patient will be deemed suitable for DIBH. For patients suitable for DIBH the breath hold AV guidance while acquiring the planning CT scan will be provided by the assigned system. The unallocated system will be set up to passively record motion. The RPM/RGSC marker block is not within the field of view of the Breathe Well camera, and the Breathe Well device does not interfere with RPM/RGSC tracking the marker block. The reference breath hold depth will be recorded for both systems.

Treatment delivery: For treatment, similarly to simulation, both systems will be set up to monitor breathing motion. The patient will be guided with AV biofeedback from the assigned system depending which arm of the trial they have been randomised to. The unallocated system will passively acquire data but not interfere with treatment in any way. Prior tests showed that no interferences and difficulties are anticipated when operating the ‘Breathe Well’ system and the RPM/RGSC system at the same time. If any treatment fraction cannot be delivered due to a failure of the Breathe Well device, this will be recorded. The treatment will continue at the physician’s discretion either (1) using the RPM system, (2) the fraction will be rescheduled or (3) delivered using free breathing.

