### Criteria for discontinuing or modifying allocated interventions {11b}

If the patient is not suitable for DIBH, the standard clinical workflow for free breathing (FB) is followed. The patient will complete the patient experience questionnaire and progress to treatment with free breathing using no breath hold management system and with no further study interventions.

Patients are entitled to withdraw consent at any time and will revert to standard of care treatment with RPM/RGSC. Outcome data for these patients will still be collected.

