### Sample size {14}

The sample size was estimated by assuming that the systematic error in treatment accuracy, Σ, will be smaller for patients on the experimental (Breathe Well) arm than the control (RPM) arm. Previously published data for a different surface monitoring system (AlignRT: VisionRT, London, UK) is given by Kanphet et al. [14] who found a systematic error of 0.46 mm in the vertical direction. For comparison, Lutz et al. [15] found a systematic error of 1.33 mm with RPM. Assuming this study will recruit a comparable patient cohort, that any differences in treatment technique will not affect the target motion, and assuming normal distribution of the systematic error in both arms of the trial and independence of the two arms, the F-test for equality of two variances estimates 36 patients will be needed for statistical significance with a power of 0.8 and alpha error probability of 0.05. The sample size for this study was set at 40 to account for an estimated 10% dropout rate for patients who cannot maintain a breath hold and are treated with free breathing.

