## Assignment of interventions: allocation

### Sequence generation {16a}

A total of 40 patients will be recruited. After an eligibility assessment and informed consent, participants will be assigned to the experimental arm or control arm with allocation ratio 1:1. The randomisation sequence and grouping will be generated by one researcher who will not be involved directly in patient screening, enrolment or assessment, and uploaded to Research Electronic Data Capture (REDCap) [16, 17]. No stratification will be utilised. The randomisation tables were set up using permuted blocks with random varying block sizes of 4 and 6.

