### Methods in analysis to handle protocol non-adherence and any statistical methods to handle missing data {20c}

Sample size estimation includes an estimation of patients who will be unable to perform DIBH.

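### The deciding 20-second breath-hold screen is run after randomisation, on the assigned device and unblinded, so the patients compared for accuracy may no longer be the groups that were randomised

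*Protocol article*

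**What the plan says.** Four parts of the protocol article bear on this.

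- **Order of steps.** Eligibility criteria {10} require the ability to hold a breath for at least 20 s. Sequence generation {16a} says: "After an eligibility assessment and informed consent, participants will be assigned to the experimental arm or control arm with allocation ratio 1:1".
- **Where the test sits.** Intervention description {11a} says: "The patients will be trained to perform DIBH with the assigned system and assessed for ability to perform a 20-s breath hold". It calls this a screening and makes suitability for DIBH depend on it. Sections {16b} and {17a} state that the arm cannot be concealed from patient or treatment team and that there is no blinding.
- **What happens to failures.** Under {11b} they complete the patient experience questionnaire and then "progress to treatment with free breathing using no breath hold management system and with no further study interventions". Sample size {14} adds 10% "for patients who cannot maintain a breath hold and are treated with free breathing". Section {11c} says that non-adherence should be recorded.
- **Analysis.** Section {20a} applies the GEE to all patients on each arm and plans no sensitivity analysis. On non-adherence and missing data, {20c} says only: "Sample size estimation includes an estimation of patients who will be unable to perform DIBH".

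On equipment failure at treatment, {11a} says: "If any treatment fraction cannot be delivered due to a failure of the Breathe Well device, this will be recorded". Such a fraction may then be given with RPM, rescheduled, or delivered in free breathing. No corresponding sentence covers an RPM failure.

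**The concern.** A criterion that should define who is randomised is applied to patients already randomised, and it is applied through the intervention itself. Coaching and test both use the allocated system, and the staff who judge the result know the arm. If one system helps weak breath-holders to pass and the other does not, one arm keeps them and the other loses them. A difference in chest wall displacement could then reflect who was left in each arm rather than how well each device holds position.

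A sample-size allowance protects power against these losses. It does nothing against selection.

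Usability is also part of the primary objective in {7}. Being unable to reach DIBH with a device is direct evidence on usability, yet no outcome in {12} and no analysis in {20a} compares that failure between arms.

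**Working it through.** **1. Are the losses counted after randomisation?** The plan needs 36 patients and allows 10% dropout: 36 / (1 − 0.10) = 40, which reproduces the stated 40. Section {16a} assigns those 40 to arms. The expected 0.10 × 40 = 4 failures are therefore the gap between 40 randomised and 36 compared. At a 10% failure rate, the chance of at least one failure among 40 is 1 − 0.9^40 = 0.985, so the situation is almost certain to arise. (Whether the F-test really gives 36 is a separate question; this point does not rest on it.)

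**2. Do failures supply primary-outcome data?** The primary outcome in {12} is displacement from the planned chest wall position on treatment images, and the hypothesis in {7} concerns position during DIBH. A patient treated in free breathing has no DIBH displacement. The sentence in {11b} that outcome data will still be collected concerns patients who withdraw consent, not those who fail the screen. Leaving the comparison is thus a strong inference, although {20a} refers to all patients on each arm.

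**3. How far could selection move a mean?** Assume a normal outcome, correlation r between breath-hold difficulty and displacement, and loss of the most difficult fraction q of one arm only. The shift in that arm, in SD units, is r × φ(c) / (1 − q), where c is the (1 − q) normal quantile.

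- q = 2/20: φ(1.282)/0.9 = 0.195, so the shift is 0.06 (r = 0.3) to 0.10 (r = 0.5).
- q = 4/20: φ(0.842)/0.8 = 0.350, so the shift is 0.11 (r = 0.3) to 0.17 (r = 0.5).

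**4. What does this do to the test?** Simulation with 20,000 trials per scenario. Every input is an assumption: 20 patients per arm, one lognormal displacement magnitude per patient (median 1 mm, log-SD 0.6), no true difference, Welch test at one-sided 5%, and the weakest breath-holders removed. The planned GEE was not simulated. All splits average the planned 10%.

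| Lost, Breathe Well vs RPM | False superiority, r = 0.3 | r = 0.5 | Bias in mean (mm), r = 0.3 to 0.5 |
|---|---|---|---|
| 20% vs 0% | 10% | 15% | −0.08 to −0.13 |
| 15% vs 5% | 7% | 9% | −0.04 to −0.06 |
| 10% vs 10% | 5% | 5% | about 0 |
| 5% vs 15% | 3% | 3% | +0.04 to +0.06 |
| 0% vs 20% | 2% | 1% | +0.07 to +0.13 |

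Negative bias favours Breathe Well. The last two rows are bias against it and would cost power if it were truly better. Equal losses are harmless here because the same kind of patient fails in both arms; equal counts alone would not guarantee that.

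**The case against.** The strongest defence is that two different tests may be meant: a simple 20-s check at eligibility, then a device-specific suitability test, which {11a} describes as a hold at 80–90% of maximal lung capacity. That reading fits {10}, {16a} and {11a} together. It does not remove the problem, because the deciding test and the budgeted 10% loss still come after assignment.

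A second defence is that the question is accuracy during DIBH, so a free-breathing patient has nothing to contribute, and that analysis sets belong in an SAP that is not shown. The first half is reasonable, but it makes the comparison conditional on passing a device-dependent screen. As to the second, the order of steps is fixed in the article itself, and {20a} expressly plans no sensitivity analysis.

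Several stronger readings are tempting, and the document does not support them:

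- *Usability information from failures is discarded.* It is not: {11b} keeps the patient questionnaire and {11c} says non-adherence should be recorded. What is absent is a by-arm comparison among the listed outcomes and analyses.
- *Device failures are recorded only for Breathe Well.* The text requires recording for Breathe Well and is silent on RPM; it does not exclude it.
- *The plan states that failures are excluded from the primary analysis.* It does not say so; this is inferred.
- *The bias favours Breathe Well.* The direction is open. Both arms receive audiovisual feedback, which may keep losses similar, and the protocol's own hypothesis that Breathe Well is more user-friendly would point to more failures under RPM.

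**Conclusion.** The concern holds as a design weakness and an internal inconsistency. Sections {10} and {16a} put the breath-hold criterion before randomisation, while {11a}, {11b} and {14} put the deciding screen and its expected 10% loss after it, on the assigned device and unblinded. As written, the plan permits device-dependent selection after randomisation, and its only stated response is the sample-size allowance.

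Neither size nor direction can be derived from the document. Under the assumptions above, false superiority at a nominal 5% runs from about 1–2% to about 10–15% across the most extreme splits of a 10% overall loss, and stays at about 5% when losses are equal and of the same kind. This shows what the design allows; it is not a prediction that the result will be biased. The point should be corrected, but it does not by itself invalidate the trial.

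**What to change.** 1. **Reconcile {10} and {16a} with {11a} and {11b}.** Do the 20-s suitability assessment before the REDCap randomisation, with the same device-neutral coaching for every patient, and randomise those who pass. Training on the assigned system then follows allocation.
2. **For any failure after randomisation,** report the number and proportion by arm as a usability outcome, and state how these patients enter the primary analysis. A rank-based analysis placing them worst is an option, but it changes the question asked and is not required.
3. **Record device failures and the system actually used, per fraction, in both arms,** and analyse fractions in the arm as randomised.

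**Cost.** Randomisation is already electronic on site, so step 1 moves it to after the assessment. On the plan's own 10%, about 40 patients would be assessed to randomise 36, or 40 / 0.9 ≈ 45 to randomise 40. The real downside is that patients who could pass only with a device screen would not be randomised, and that some device-specific failures would no longer be seen. Steps 2 and 3 need one table, one sentence on the analysis set and one extra data field. They remain possible if recruitment has already closed, as far as the data were recorded; step 1 does not.
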